## Abstract

**Background:**

Multiple chemical sensitivity (MCS) is a condition characterized by recurrent, self-reported symptoms from multiple organ systems, attributable to exposure to a wide range of chemically unrelated substances at low levels. The pathophysiology is unknown, and affected individuals generally favor avoidance of the symptom triggering substances as a coping strategy. The impact of MCS on daily life may thus be severe. An intervention that may effectively reduce the impact of MCS, alleviate the symptoms and the psychological distress associated with the condition is therefore highly needed. In this study we will assess the effects of a mindfulness-based cognitive (MBCT) program on MCS.

**Methods/Design:**

Using a randomized controlled design (RCT), we will compare MBCT with treatment as usual (TAU). The MBCT intervention will include 8 weekly 2.5 hour sessions, and 45 minutes of mindfulness home practice 6 days each week. Participants will be asked to complete questionnaires at baseline, post-treatment, and at 6 and 12 months’ follow-up. Based on sample size estimation, 82 participants will be randomized to either the MBCT intervention or to TAU. The primary outcome will be a measure of the impact of MCS on the participants’ lives. The secondary outcome measures are physical symptoms of psychological distress, perceived stress, illness perceptions, QOL, and work ability. Lastly, we will assess whether any effect of MBCT on the primary effect measure is mediated by level of mindfulness, self-compassion, perceived stress, and rumination.

**Discussion:**

This trial will provide important information on the effects of MBCT on MCS.

**Trials registration:**

Clinical trials identifier NCT01240395

## Background

The term ‘multiple chemical sensitivity’ (MCS) is applied to a condition of recurrent, self-reported symptoms from multiple organ systems. Other labels have been ascribed to the symptoms, but MCS is widely used in the scientific literature, and thus, will be used here without reference to any assumptions about etiology. The symptoms follow perceived exposure to a wide range of airborne chemicals at levels normally considered non-toxic [1]. Frequently reported symptom-eliciting chemicals and environmental agents include fragranted products, motor-vehicle exhaust fumes, cleaning agents, freshly printed papers or magazines, and smoke from wood burners [2,3]. A recent population-based study showed that extreme fatigue, headache, gastrointestinal symptoms, muscle and joint pain, upper airway symptoms, and irritability are the most frequently reported symptoms [3]. It has been documented that symptoms from the central nervous system (CNS) other than headache are the single most predictive factor of the severity of MCS [2]. Despite the limited number of studies investigating syndrome stability in MCS, evidence points to MCS being a chronic condition [4,5].

The pathophysiological mechanisms behind MCS remain unknown [6,7]; however, current evidence suggests that MCS is more likely to be due to individual susceptibility factors than to a toxicological response to common airborne chemicals [7,8]. Moreover, recent evidence indicates that sustained levels of arousal may be a risk factor in the development of MCS [9]. Several underlying mechanisms have been proposed, such as sensitization of the CNS [10,11], and symptom acquirement due to classical conditioning [12,13]. Increased levels of depression, anxiety, and somatization, are frequently reported [14-17], and it has thus been suggested that MCS belongs to a spectrum of somatoform disorders [18]. However, evidence supporting this view is sparse.

Provocation studies examining responses of individuals with MCS when exposed to either active or sham provocation have found that, in general, these individuals cannot differentiate between active and sham exposures, symptomatically or otherwise. While the mechanisms by which airborne chemicals trigger MCS symptoms are unclarified, the significance of mental representations of illness has been found to be particularly influential in patients presenting with medically unexplained symptoms, in terms of onset, persistence of symptoms, and degree of disability [19], when comparing a medically unexplained illness with an illness of known physiological origin [20].

Currently, there are no evidence-based treatments or clinical guidelines for MCS [21,22]. A typical coping response seems to be that of avoiding potential chemical triggers, typically through the creation of a safe living space and the application of protective routines, thus avoiding exposure to symptom-eliciting stimuli [23,24]. However, this may come at a cost, because several aspects of the patients’ everyday life, including lifestyle, social relations, and occupational conditions, are affected by the behavior [23]. Considering the impact MCS has on the lives of those affected, an effective evidence-based treatment is urgently needed.

Mindfulness, defined as ‘the awareness that emerges through paying attention on purpose, in the present moment, and non-judgmentally to the unfolding of experience moment by moment’ [25], is becoming increasingly popular, and mindfulness-based interventions show promise in the treatment of stress-related medical disorders [26]. It has been suggested that mindfulness-based interventions could be useful in the treatment of such disorders by improving disease management and reducing psychological distress, thereby improving wellbeing [27].

A few clinical trials have assessed the effect of mindfulness-based therapy on conditions with hypothesized shared illness mechanisms and a high degree of co-morbidity to MCS; such as fibromyalgia [28,29], irritable bowel syndrome [30] and chronic fatigue [31]. Although the results of these studies are inconclusive, the findings are generally positive, warranting larger randomized clinical trials (RCTs).

One study, applying a non-randomized waiting-list design, evaluated the effect of a mindfulness-based intervention program on participants with MCS with various types of co-morbidity to other functional disorders [32]. The results showed that the mindfulness-based intervention was associated with a significant decrease in symptoms of somatization and psychological distress compared with the waiting-list control group. However, the study did not include outcome measures directly related to the participants’ MCS, so it is uncertain whether the intervention had any effect on this outcome. The feasibility of a MBCT program for MCS was tested in a recent randomized pilot trial. The study concluded that a group intervention was feasible for MCS and a larger randomized trial could be considered [33].

### Objectives

The main aim of the proposed study is to evaluate whether an 8-week mindfulness-based intervention program is associated with a reduction in the degree to which MCS affects participants’ lives (for example, ability to travel, to be around others and to enjoy social activities). The secondary aims are to evaluate whether the intervention is associated with a reduction in commonly experienced symptoms (for example, muscle or joint aches, headache, difficulty in concentrating), severity of reactions to common chemicals, psychological distress (anxiety, depression, and somatization), and perceived stress, and whether the intervention increases participants’ quality of life (QOL) and work ability. The study will also assess whether the intervention affects the participants’ illness perceptions. Finally, it will assess whether degree of mindfulness, stress, self-compassion, and rumination are possible mediators of a treatment effect.

#### Hypotheses

The primary hypothesis is that the degree to which MCS affect participants’ daily lives will be significantly reduced in the mindfulness intervention group compared with the control group. The secondary hypotheses are 1) that we expect a significant alleviation of MCS symptoms, symptoms of depression, anxiety, somatization, and perceived level of stress, thereby improving overall psychological wellbeing compared with that in the control group, and 2) that the mindfulness intervention will lead to positive changes in illness perception and will improve QOL and work ability.

In terms of mediating treatment mechanisms, we expect that a treatment effect will be mediated by the level of mindfulness, as was found in a previously conducted trial with participants with a similar level of disability [30]. Additionally, we will assess whether self-compassion, which was recently found to mediate a reduction in depressive relapse [34], also mediates a treatment effect in our group of patients. Moreover, and in line with a previous prospective study that established prolonged stress as a risk factor in the development of symptoms [9], we will investigate whether the reverse is also true; that is, whether a reduction in the level of stress is associated with a reduction in the degree to which chemicals affect participants’ daily lives. Furthermore, we will explore whether a positive change in illness perceptions (for example, a greater sense of control, an increased sense of understanding of MCS, and a reduction in the concern associated with MCS) will mediate a treatment effect. Lastly, recent research suggests that rumination could be a transdiagnostic factor underlying several psychiatric conditions [35], and we will investigate whether it is also a possible mediator of a treatment effect for individuals with MCS.

## Methods/Design

### Empirical design

The study is an RCT in which the effect of a mindfulness-based intervention program will be compared with that of a TAU control group. Because this is a pragmatic trial, we will enhance the external validity by keeping exclusion criteria to a minimum. The study will be undertaken in the cities of Copenhagen and Aarhus, Denmark.

### Participants

Participants will be recruited through several sources. First, we will contact GPs in the Copenhagen and Aarhus areas and provide them with information about the study. Second, we will contact individuals with MCS registered at the Danish Research Centre for Chemical Sensitivities who have agreed to be contacted about research projects, and invite them to participate in the study. Lastly, we will advertise the study on the website of the Danish Research Centre for Chemical Sensitivities, in patient magazines, and in local newspapers.

### Inclusion criteria

Participants will need to be aged 18 to 65 years, and provide written, informed consent. They will need to fulfill the expanded consensus criteria for MCS [36,37], as follows. 1) The condition has lasted for at least 6 months causing significant lifestyle or functional impairments; 2) there are reproducible CNS symptoms and 3) at least one symptom from another organ system; 4) the symptoms occur in response to low levels of exposure to 5) multiple unrelated chemicals and 6) improve or are resolved when these inciting substances are removed.

### Exclusion criteria

The exclusion criteria are: presence of 1) a psychotic or bipolar disorder, 2) suicidal ideations, 3) drug or alcohol abuse; and 4) previous engagement in a mindfulness-based intervention program.

### Assessment

Before randomization, all participants will be assessed, using the Schedules for Clinical assessment in Neuropsychiatry (SCAN), an instrument to assess and classify the psychopathology and behavior associated with major psychiatric disorders. The interview contains an extensive section on somatic symptoms, providing an opportunity to obtain an overview of the participants’ symptoms from various organ systems. We will also use SCAN to assess whether the participants fulfill the criteria for various other functional somatic syndromes, applying the SCAN algorithms suggested by Fink and Schröder [38]. Classification of such syndromes will be based solely on the interview rather than by a thorough medical investigation, as the purpose is purely descriptive. Lastly, the SCAN interview will be used to identify subjects who present with severe psychopathology, and who thus will be excluded from participation.

Concerning the specific needs that chemically intolerant people may have in terms of environment, eligible participants will be asked to consider whether they are able to engage in a group setting and to refrain from using fragranced products while attending the classes.

### Randomization

The randomization will be carried out as follows. Once we have recruited 16 to 20 eligible participants (the number of participants required to start off a MBCT group) who have signed a written consent form, they will be randomized by a computer-generated allocation sequence either to intervention with MBCT or to the TAU control condition. The randomization will be pre-programmed so as to produce equal numbers in both groups. The randomization procedure will be carried out at the Research Centre for Chemical Sensitivities by a researcher who is otherwise not involved in the trial, thus securing concealment to the research team. Once the randomization has been carried out, the first author will contact participants by telephone and email to inform them about the allocation.

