### Statistical analysis

Statistical analyses will be conducted using the latest version of SPSS. Group allocation (intervention or control) will be concealed for the statistician who will perform the statistical analyses. Descriptive statistics for the two groups will be generated. In the statistical analyses of a possible effect, the mixed model repeated measures method will be used to test the effect of the intervention and the effect of time. Level of significance will be set at *P* < 0.05. All effect measures will be inspected for normality, and transformed as appropriate. Missing values will be handled by the multiple imputation method. Data analysis will be performed based on the intention-to-treat principle, meaning that all participants will be included in the analysis irrespective of their compliance with the intervention protocol. Lastly, an additional per-protocol analysis will also be conducted.

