### Sample size

The sample size estimation is based on the primary effect measure, the QEESI. Results from a recently conducted study evaluating a Danish translation of the QEESI, showed that the patient sample had a mean value of 61.5 with a standard deviation of 24.3 on the LIS [43]. In this study, a clinical effect will be set as a 25% reduction on the LIS of the QEESI, which we regard as a clinically meaningful reduction in the effect of MCS on participants’ daily lives. With a reduction of 25% on the LIS, the study will need to include 41 experimental subjects and 41 control subjects to be able to reject the null hypothesis, that is, that the population means of the experimental and control groups are equal with probability (power) of 0.8. The type I error probability associated with this test of this null hypothesis is 0.05.

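### Participants are randomised in balanced recruitment batches, but the described model names no batch term; adding one is a small, almost free correction to the standard error

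*Protocol article*

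**What the plan says.** Allocation (protocol article, Randomization) happens in batches: "Once we have recruited 16 to 20 eligible participants (the number of participants required to start off a MBCT group" and these have consented, a computer-generated sequence assigns them to MBCT or usual care. On balance the section says: "The randomization will be pre-programmed so as to produce equal numbers in both groups". It does not say whether equality is forced in each batch or only over the whole trial.

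On location (Empirical design): "The study will be undertaken in the cities of Copenhagen and Aarhus, Denmark". No section says that a batch is drawn from one city.

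On analysis (Statistical analysis): "the mixed model repeated measures method will be used to test the effect of the intervention and the effect of time". Neither batch nor city is named, and neither is excluded.

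On size (Sample size): "the patient sample had a mean value of 61.5 with a standard deviation of 24.3 on the LIS", and "a clinical effect will be set as a 25% reduction on the LIS of the QEESI", from which "the study will need to include 41 experimental subjects and 41 control subjects" at a power of 0.8 and a type I error of 0.05. The calculation compares two independent groups.

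**The concern.** When each batch is split equally between the arms, whatever distinguishes one batch from another (recruitment period, and probably city) falls equally on both arms and drops out of the difference. An analysis without batch leaves that variation in the error term. The estimate is right, but its standard error describes a less efficient design than the one that was run. The result is an interval that is somewhat too wide, a type I error rate somewhat below 0.05 and a small loss of power. A two-arm trial of 82 participants has little power to spare, and the remedy needs only information already on the randomisation list.

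**Working it through.** **Inputs from the protocol article.** Life Impact Scale (LIS) mean 61.5 and SD 24.3, target reduction 25%, 41 per arm, power 0.8 and alpha 0.05 (Sample size); batches of 16 to 20 (Randomization). **Assumed:** the between-batch share of LIS variance, rho, from 0 to 0.10, because no document gives it.

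**1. The plan's own figure.** Difference = 0.25 × 61.5 = 15.375 points; standardised, 15.375/24.3 = 0.633. Two-sided at 0.05 with power 0.80, the normal approximation gives 40 per arm. The t-test gives 40.2, rounded up to 41. The stated 41 reproduces. Power at 41 per arm is 0.808 by t-test.

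**2. Number of batches.** 82/20 = 4.1 and 82/16 = 5.1, so about 4 to 5. Five fits if every batch stays within 16 to 20: for example 16 + 16 + 16 + 16 + 18 = 82, with halves 8 + 8 + 8 + 8 + 9 = 41. A batch of 16 to 20 split equally gives an MBCT class of 8 to 10, which supports reading the balance as per batch.

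**3. Standard error with and without batch (five batches, single follow-up, total SD fixed at 24.3).**
- True SE of the arm difference = 24.3 × sqrt(1 − rho) × sqrt(2/41).
- A model without batch estimates, on average, the variance 24.3² × [(1 − rho) + rho × 82 × (1 − 1/5)/80] = 24.3² × (1 − 0.18 rho).
- Ratio of reported to true SE = sqrt((1 − 0.18 rho)/(1 − rho)).

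Power without batch is the normal probability of (15.375/true SE − t critical value × ratio). With batch it comes from the noncentral t with 76 degrees of freedom.

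| rho (assumed) | True SE | SE reported without batch | Ratio | Power without batch | Power with batch |
|---|---|---|---|---|---|
| 0 | 5.367 | 5.367 | 1.000 | 0.809 | 0.807 |
| 0.02 | 5.313 | 5.357 | 1.008 | 0.813 | 0.815 |
| 0.05 | 5.231 | 5.343 | 1.021 | 0.818 | 0.827 |
| 0.10 | 5.092 | 5.318 | 1.045 | 0.827 | 0.846 |

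Power rises down the table because total variance is held at the stated SD, so a larger batch share means less variance within batches. Four batches give nearly the same ratios (1.008, 1.020, 1.042).

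**4. Simulation (20,000 runs, five batches).** Type I error without batch was 0.046, 0.047 and 0.042 at rho 0.02, 0.05 and 0.10. With batch it was 0.049 to 0.051.

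**5. Effect of baseline.** The LIS is also measured at baseline. If baseline is a covariate with an assumed correlation r to follow-up, a stable batch share rho leaves a residual share of rho × (1 − r)/(1 + r). At r = 0.6 and rho = 0.10 this is 0.10 × 0.4/1.6 = 0.025. The SE excess is then sqrt((1 − 0.18 × 0.025)/(1 − 0.025)) = 1.010, so 1.0% in place of 4.5%. In change from baseline, a stable batch difference cancels altogether.

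**6. Clustering by MBCT class.** MBCT is taught in groups, in one arm only. The simulation added a class share of 0.02, 0.05 or 0.10 to rho = 0.05. Type I error was then 0.056, 0.066 and 0.092 without batch, and 0.061, 0.073 and 0.102 with fixed batch effects.

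**The case against.** The strongest reply is that this argues from silence. The Statistical analysis section states which effects will be tested; it does not list every model term. A journal article condenses the full protocol, and blocking factors are often left to an analysis plan that is not shown here. That stands: a reader might infer that the analysis will ignore batch, but the article does not say so. What remains is that the only model described does not mention a central feature of the allocation, and that naming it costs almost nothing.

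A reader might also infer that batch means city and recruitment source. A weekly class drawing on both Copenhagen and Aarhus is unlikely, so city is a plausible component, but no section says that batches are formed within one city. Only period follows directly from randomising each batch as it fills.

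The size is also open to challenge. The table treats a single follow-up without baseline, whereas the plan is a repeated-measures model. Step 5 shows that stable batch differences shrink or vanish once baseline is used, so the table is an upper range for stable differences. A batch main effect would add almost nothing to a group-by-time test with baseline among the responses. This is accepted and shapes the fix.

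Finally, a reader might conclude that the trial's standard error is too large overall. Step 6 shows why that does not follow: class clustering pushes the other way, and a fixed batch term alone moves the type I error slightly further from 0.05.

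**Conclusion.** The point holds as a minor improvement. If equal numbers are forced within each batch and batch is left out of the model, the standard error is too large by about 0.8, 2.1 or 4.5% at an assumed between-batch share of 2, 5 or 10%. At most about 2 points of power are lost (0.827 against 0.846), and less once baseline LIS is accounted for. Power stays above the planned 0.80 throughout these cases, before any class clustering. The omission errs on the conservative side. It does not bias the estimate, change the stated 41 per arm or invalidate the analysis.

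The direction is secure given balance within batches. The size rests on an assumed variance share and is zero if batches do not differ.

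**What to change.** State that equal allocation is forced within each recruitment batch, if that is so, and name randomisation batch as a fixed factor in the primary and secondary models. If baseline is a covariate, enter batch as a main effect. If baseline is one of the repeated responses, include batch-by-time, because a main effect alone would do almost nothing for the group-by-time comparison.

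The cost is wording and about four of 80 degrees of freedom (five levels, leaving 76). If batch has no effect, power falls by about 0.002 (0.809 to 0.807). No new data are needed. If the full analysis plan already contains the term, nothing changes.

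Clustering by MBCT class should be handled by its own term, specified alongside batch. The article names no such term. Its cost is separate and larger: with about five classes, few degrees of freedom are left for the arm comparison.

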### Intervention

The mindfulness-based intervention in this RCT is modeled on MBCT, which is a group skills-based training approach developed to prevent relapse of depressive episodes [39]. MBCT is partly based on the mindfulness-based stress reduction (MBSR) program developed by Kabat-Zinn [40], and partly on cognitive therapy for depression. MBCT focuses on the aspect of ‘de-centering’, meaning not accepting the content of thoughts as facts and not identifying with thoughts [39]. The MBCT program has been fully manualised by Segal and colleagues, describing the exercises and rationale in detail [41]. However, as the original program was developed to prevent relapse of depression, some minor modifications will be made to the curriculum in this trial to adapt it for individuals with MCS. For example, session seven in the MBCT program deals with identifying signs of depressive relapse, but in our study, the emphasis will be on applying mindfulness in coping with stress. The main treatment component will be mindfulness exercises, which includes various forms of meditation and yoga. The purpose of the mindfulness exercises is to cultivate the ability to stay in the present with full awareness, and to practice an attitude of acceptance of whatever sensation, pleasant or unpleasant, that arises in the present moment. Before commencing the program, all the participants will be invited to an individual session with the group therapist with the aim of getting to know the participants and answering questions about the program. The program will be given to groups with a maximum of 15 participants, and will comprise eight weekly sessions, each 2.5 hours long, plus a half-day of silent retreat between weeks 6 and 8. Additionally, during the program, participants will be encouraged to do home work assignments of up to 45 minutes 6 days a week. Guided instructions will be provided on a CD for home practice. If a participant is unable to attend a session, they will be e-mailed any written material handed out during the class. Finally, participants will be offered follow-up sessions at months 1, 3, and 6 post-treatment.

The therapists teaching mindfulness in the trial will be two clinical psychologists, both of whom have extensive experience in delivering mindfulness-based treatment. They have undergone formal education in mindfulness-based therapies from The Oxford Mindfulness Centre and from the Umass Centre for Mindfulness in Medicine, Healthcare, and Society, respectively.

